### Questionnaires

3.3

At week 0 and week 6, as well as during the follow-up period, the examiner will work closely with the patient to fill in this Timeline Follow Back (TLFB) schedule for the past month, based on the alcohol diary collected weekly. The TLFB has been widely evaluated and tested,^[19]^ and in previous studies,^[20]^ it has been proved to have high retest reliability. The data collected by TLFB will be applied to evaluate the effects on the primary outcomes and secondary outcomes.

Baseline data for the Clinical trial, the Alcohol Use Disorders Identification Test (AUDIT) questionnaire, the TLFB interview, and the diagnostic instruments or questionnaires for diagnosis of alcohol addiction will be collected routinely for all patients. At week 0 and week 6, as well as during the follow-up period, the questionnaires will be conducted including: demographics (age, gender, marital status, occupation), alcohol consumption (TLFB), withdrawal symptoms (CIWA-Ar), alcohol addiction (MAST), craving (Pennsylvania Alcohol Craving Scale (PACS)), drinking behaviors (AUDIT), health status (SF-36), psychopathology (Symptom Checklist (SCL-92)),drug use (DUDIT), and adverse events (COMBINE Systematic Assessment For Treatment Emergent Events (COMBINE SAFTEE)).

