### Recruitment

2.3

The patients will be recruited from the outpatient or inpatient department of the Affiliated Hospital of Chengdu University of Traditional Chinese Medicine. The clinicians participating in the withdrawal treatment unit will conduct preliminary screening of patients in the inpatient or outpatient department, and briefly describe the study to the patients who meet the criteria. If the patients are interested in participating, the clinician will alert the research team. A member of the research team will provide them with a comprehensive oral and written description of the research's aims and procedures and the research team members will understand their rights and responsibilities while participating in the study. Screening examinations only be performed after they have agreed to participate and signed the informed consent form. During screening, the patients will undergo related examinations to make sure that all inclusion criteria and none of the exclusion criteria are met.

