1.Neuronal degeneration with irreversible process or severe psychiatric disease, for example, a diagnosis of paranoid psychosis, schizophrenia, mental retardation, or bipolar disorder.2.Concomitant drugs therapy against alcohol dependence, such as naltrexone, disulfiram, nalmefene and acamprosate, or other treatment with any of the drugs within 1 month prior to inclusion.3.Concomitant pharmacotherapy with psychotropic medications such as antipsychotics, antiepileptics, mood stabilizers, carbonic anhydrase inhibitors, opioid analgesics, or systemic steroids before enrollment (drug elution periods are allowed, depending on the pharmacokinetic characteristics of the drug).4.Drug Use Disorders Identification Test (DUDIT) score >6 (male), >2 (female), and meeting the substance dependence standards of ICD-10 (except nicotine and caffeine).5.Psychological treatment for mental disorder within the preceding 3 months.6.Having more than 4 unsuccessful hospitalizations for alcohol withdrawal in the past.7.Patients who met the diagnostic criteria of alcohol dependence and had been completely abstinent for more than 2 months.8.Patients who are allergic to ASF.9.Pregnant women, those who plan to become pregnant within 3 months and lactating women.10.Severe physical diseases, including uncontrolled hypertension, cerebrovascular diseases, pulmonary diseases, thyroid diseases, etc (uncontrolled hypertension (systolic blood pressure >180 mm Hg, diastolic blood pressure >110 mm Hg)).11.Those who are preparing for surgery or organ transplantation recently.12.Those who cannot conduct the test as required.13.Severe heart, hepatic and renal dysfunction, or other severely abnormal laboratory tests (cardiac problems defined as decompensated heart failure (New York Heart Association functional class III or IV)), myocardium infarction within the past 12 months and/or unstable angina pectoris; impaired hepatic function (liver transaminases >3 the upper limit of normal); impaired renal function (estimated glomerular filtration rate (eGFR) <60 mL/min); kidney stones; pancreatitis, etc).14.Participants in other drug trials within the last 4 weeks.

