### Outcome measures

3.2

Primary outcomes: The primary outcomes are the changes in the average daily alcohol consumption of the 2 groups before and after treatment and comparison of the scores of the psychological craving self-rating scale during the courses of treatment of 2 groups.

Secondary outcomes: The secondary outcomes include abstinence rates of the 2 groups during the follow-up period, days without consumption, and changes of Short Form Health Survey (SF-36) scores in 2 groups before and after therapy.

The researchers will use weekly self-reports during the follow-up period, clinicians’ judgments, and biochemical examinations to determine whether the patient is abstinent. If the patient has drunk no more than 1 cup since the last visit, the GGT level is normal, or has not increased since the last examination, and the respiratory alcohol concentration is less than 0.10 g/L, the patient is judged to abstain from alcohol.

From the first week to the sixth week, vital signs will be monitored daily. The physical examination will be carried out weekly. The respiratory alcohol concentration will be measured once a week, and drinking craving and adverse events will be evaluated weekly at the time of enrollment and at weeks 2, 4, 6, and 7, serum γ-glutamyl transpeptidase (γ-GT) and blood alcohol concentration will be detected. At weeks 0, 3, and 6, the doctors will give the patients electrocardiograms, and urine pregnancy, blood routine and blood biochemical levels will be detected. During the follow-up period, serum γ-GT and respiratory alcohol concentration will be measured once a week.

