### Compliance

3.5

During the treatment phase, the researchers will record the type, frequency, and dose of any drug received by the patient during the hospitalization, monitor the patient's medication compliance ((drug bags distributed-returned bags)/total number of prescription bags) and other medications taken during the treatment period, and copy any relevant clinical records made at the time of admission. Another researcher who does not participate in the training management and is blinded to the treatment allocation of the patients will contact follow-up interviews including abstinence and TLFB, during the follow-up period after treatment. According to the intention-to-treat principles, patients who withdraw from treatment will still be contacted by researchers for follow-up before completing the 6 weeks of treatment, unless they withdraw from the study.

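### The baseline for the consumption primary covers one month, but patients abstinent for up to two months are eligible, so for some patients the change score cannot show a reduction from usual drinking.

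*Protocol article*

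**What the plan says.** Section 3.2 (Outcome measures) names two primary outcomes. One is "the changes in the average daily alcohol consumption of the 2 groups before and after treatment"; the other is the craving score.

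Section 3.3 (Questionnaires) says how drinking is measured. At week 0, at week 6 and during follow-up, the examiner and patient are to "fill in this Timeline Follow Back (TLFB) schedule for the past month, based on the alcohol diary collected weekly". It adds: "The data collected by TLFB will be applied to evaluate the effects on the primary outcomes and secondary outcomes". No other baseline window is given, and no diary phase before enrolment is described.

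Section 2.8 (Eligibility criteria), exclusion 7, removes "Patients who met the diagnostic criteria of alcohol dependence and had been completely abstinent for more than 2 months". The inclusion criteria cover age, diagnosis, withdrawal status (CIWA-Ar below 15), a MAST score above 7 and consent. None sets a minimum amount or number of days of recent drinking.

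Section 2.3 (Recruitment) admits both settings: "The patients will be recruited from the outpatient or inpatient department". Section 3.8 (Statistical analysis) compares continuous variables between groups with an independent-sample t test and mentions no adjustment for baseline consumption or setting.

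**The concern.** A change in consumption from before to after treatment is naturally read as reduction from usual drinking. That reading needs a baseline taken while the patient was still drinking. Here the look-back is half as long as the abstinence that eligibility allows, so some patients can enter with a baseline that describes their recent abstinence and not their habit.

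For such a patient, staying abstinent to week 6 is the best possible result, yet it is recorded as no change. Two patients with the same usual intake also receive different baselines if they stopped on different dates. At stake are the meaning of one of the two primary outcomes and the value of the baseline measurement in the analysis. Once week-0 data have been collected over the wrong window, they are hard to recover.

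**Working it through.** **The plan's own figure.** The only sample-size calculation (section 2.4) uses withdrawal rates of 54.5% and 16.7% and gives 34 per arm. The standard two-proportion formula gives 32 per arm, or 37 with continuity correction, so 34 is plausible. It contains no mean or SD for consumption and so cannot size the present problem.

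**Inputs**
- Look-back window: one month, taken as 30 days (section 3.3).
- Longest eligible abstinence: two months, taken as 60 days (section 2.8, exclusion 7).
- Minimum recent drinking: none stated (section 2.8).
- Illustrative assumption: before stopping, the patient drank a steady amount c per day.

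**Step 1: baseline as a function of dry days.** With k dry days immediately before week 0, the measured baseline is

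B(k) = c × (30 − k)/30 for k up to 30, and B(k) = 0 for k from 30 to 60.

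| Dry days k | Measured baseline | Cut from usual intake |
|---|---|---|
| 0 | c | 0% |
| 14 | c × 16/30 = 0.53c | 14/30 = 47% |
| 21 | c × 9/30 = 0.30c | 21/30 = 70% |
| 30 to 60 | 0 | 100% |

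Every row is eligible under exclusion 7.

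**Step 2: the change score at zero baseline.** Change = post − B. With B = 0 and post at least 0, change is 0 or positive. A patient who stays dry scores 0. A patient with k = 0 who halves intake scores −c/2.

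**Step 3: the comparison of arms.** The expected difference in mean change is

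[E(post, ASF) − E(post, placebo)] − [E(B, ASF) − E(B, placebo)].

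Under 1:1 randomisation the second bracket is zero in expectation, whatever the mix of dry days. A low or zero baseline therefore neither biases nor shrinks the expected contrast between arms. That contrast depends on post-treatment drinking.

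**Step 4: the baseline as a covariate.** Because B(k) mixes usual intake c with dry days k, it does not separate heavy from light drinkers. At k of 30 or more it is 0 for every value of c and carries no information on usual intake.

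**The case against.** The strongest reply is that randomisation protects the trial. Step 3 shows that this is right: the arms are compared without bias. Ranking one abstinent patient below a heavy drinker who halves intake says nothing about the difference between arms. This part of the objection stands.

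A reader might infer a calculable loss of power by treating patients with zero baseline as carrying no treatment effect. The documents do not support that. Such patients can relapse, and section 4 (Discussion) presents reducing relapse as a purpose of ASF, so they can carry treatment signal. With an assumed effect of 0.80 SD, 34 per arm and an assumed quarter of patients affected, power would be 68%, 81% or 90% according to whether these patients carry none, half or all of the effect. The documents fix none of these assumptions, so no figure from that range belongs in the finding.

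A reader might also infer that the outcome reflects ward stay as much as ASF. Section 3.5 (Compliance) does refer to the "dose of any drug received by the patient during the hospitalization". However, no length of stay is given, and nothing says that inpatients are already dry at entry. Confinement would also act differently: someone who drank until admission and is then confined shows a large reduction in either arm, not zero change.

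There is partial mitigation. The craving primary does not depend on this window, abstinence rates and days without consumption are secondary outcomes, and TLFB is repeated in follow-up. The benzodiazepine provision for severe withdrawal symptoms suggests that recent drinkers are also expected, so the group dry for a full month may be small.

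Finally, covariate adjustment is commonly left to an analysis plan, which is not shown. That is fair for the adjustment alone. It does not answer the mismatch, since both the window and the abstinence limit are fixed in the text. None of these points gives a baseline in usual drinking to a patient who stopped more than a month ago.

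**Conclusion.** The mismatch is on the face of the protocol and nothing else in it resolves it. Patients dry for about 30 to 60 days have a consumption baseline of 0 and can show only no change or an increase. Patients dry for less time have a baseline lowered in proportion, by 47% at 14 days and 70% at 21 days for a previously steady drinker on a 30-day month.

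The harm is limited to interpretation and to the usefulness of the baseline. In these patients the change score is not a reduction from usual drinking, and the baseline is a weak or empty covariate. The comparison between arms remains unbiased, and only the consumption primary is affected. The overall size cannot be computed, because the documents give neither the distribution of dry days at entry nor the mean and SD of consumption. The point is worth correcting before week-0 data are collected, but it does not invalidate the randomised comparison.

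**What to change.** Reconcile section 3.3 with exclusion 7 in section 2.8:

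1. Set the baseline TLFB window to the month before the last drink, or before admission if that is earlier. The week-6 and follow-up windows can stay as they are.
2. Compare arms on post-treatment average daily consumption, adjusted for that baseline and for inpatient or outpatient status (analysis of covariance), in place of an unadjusted t test on change.

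Keep all post-treatment days in the outcome. Counting only days outside hospital would condition on discharge, which treatment may affect, and would leave anyone hospitalised throughout the window without a value.

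The cost is a revised TLFB instruction and revised outcome and analysis wording. The downside is longer recall: up to 2 months of abstinence plus a 1-month window reaches back about 3 months, with no pre-enrolment diary described to support it.

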### Design

2.1

The study is a 6-week randomized, controlled, prospective, double-blind clinical trial. After obtaining informed consent, the 82 alcohol-dependent patients recruited will be randomly divided into the ASF group and the placebo group according to 1:1. The study will include a 6-week treatment period and a 12-week follow up time. Both groups of patients will receive psychosocial alcohol therapy and some conventional symptomatic treatments such as liver protection. Besides, for those with severe abstinence symptoms during abstinence, benzodiazepines can be given as appropriate. On this basis, patients in the ASF group will be treated with 1 dose of ASF 3 times a day, while the control group will receive placebo treatment. The purpose is to evaluate the efficacy and tolerability of ASF in treating patients with alcohol dependence and explore the action mechanism of ASF. The protocol is presented in line with the Standard Protocol Items: Recommendations for Interventional Trials 2013 statement (the SPIRIT figure for the schedule of enrollment, interventions, and assessments is presented in Fig. 1; the checklist of SPIRIT is in Supplemental file 1). The diagram of the study flow is shown in Figure 2.

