### Sample size

2.4

This study adopts a randomized, controlled, double-blind clinical trial design. Based on data from the study by Johnson et al,^[18]^ where withdrawal rate was 54.5% in the treatment group and16.7% in the control group, with an alpha of 5%, and a power of 90%, the estimated sample size for the 2 groups was 68 patients using the PASS 15 software (34 patients in each group). With an estimated dropout rate of 20%, a total number of 82 patients (41 patients in each arm) will be needed.

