### Statistical analysis

3.8

Data analysis will be performed using the SPSS 18.0 statistical software package. Categorical variables will be compared by use of chi-square analysis. Continuous variables between groups will be analyzed by independent sample *T* test. The repeated measure of analysis of variance (ANOVA) will be used to analyze the differences in the group. For all reported values will be expressed as mean ± SEM. The log-rank test will be applied to compare the cumulative probability functions. The Cox proportional hazards model will be applied to assess the hazard ratio of achieving 12 weeks of abstinence and the Kaplan–Meier method will be used to calculate the cumulative probability function of reaching 12 weeks of abstinence. The changes of desire measured by PACS will be compared at baseline and at week 6 through the *T* test. The changes of desire and resistance during the study will be analyzed by using mixed linear regression analysis. All statistical tests will be two-sided tests, and *P* < .05 indicates that the difference is statistically significant.

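### The craving co-primary covers the course of treatment, but the text places PACS, the only craving scale it names, at just weeks 0 and 6 of treatment, and neither planned craving analysis is marked primary

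*Protocol article*

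**What the plan says.** All references are to the protocol article.

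- **Section 3.2, Outcome measures.** One of the two primary outcomes is "comparison of the scores of the psychological craving self-rating scale during the courses of treatment of 2 groups". The scale is not named. On timing, the same section says "drinking craving and adverse events will be evaluated weekly at the time of enrollment and at weeks 2, 4, 6, and 7", after which the sentence goes on to serum γ-GT and blood alcohol concentration.
- **Section 3.3, Questionnaires.** The timing is "At week 0 and week 6, as well as during the follow-up period, the questionnaires will be conducted including", and the list that follows contains "craving (Pennsylvania Alcohol Craving Scale (PACS". No other craving scale is named anywhere in the text, including the Figure 1 legend.
- **Section 3.8, Statistical analysis.** Two craving analyses are planned. The first is a t test: "The changes of desire measured by PACS will be compared at baseline and at week 6 through the" t test. The second is a model: "The changes of desire and resistance during the study will be analyzed by using mixed linear regression analysis". No instrument is named for resistance, no visits are given for the model, and neither analysis is called primary.
- **Section 2.1, Design.** "The study will include a 6-week treatment period and a 12-week follow up time".

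**The concern.** A primary outcome needs one instrument, one set of visits and one primary analysis. For craving, each of these depends on which section is followed. If staff work from Section 3.3 alone, PACS is completed at entry and at the end of treatment, and the weekly evaluation in Section 3.2 is done in some other, unspecified way or not at all. Scores not collected in weeks 1 to 5 cannot be recovered by a later analysis plan, so this has to be settled in the protocol and not deferred.

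The second risk is selection. Two analyses, and possibly two measures, compete for the same co-primary outcome, each tested at P < .05. Unless one is fixed beforehand, the choice can follow the result. This matters more here because the Introduction gives reduced craving as the hypothesised mechanism of the treatment.

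**Working it through.** The plan gives no figure to reproduce. The check sets the sections side by side and counts craving scores within the 6-week treatment period.

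**Possible readings**

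| Reading | Measure | Scores in treatment after baseline |
|---|---|---|
| Section 3.3 taken literally | PACS at weeks 0 and 6 | 1 (week 6) |
| Section 3.2, weekly, scale assumed to be PACS | PACS at week 0 and weeks 1 to 6 | 6 |
| Section 3.2, weekly, scale not PACS | PACS at weeks 0 and 6, plus an unnamed weekly measure | 1 on PACS, 6 on the other |
| Section 3.2, listed weeks attached to craving | enrolment and weeks 2, 4, 6 and 7 | 3 (weeks 2, 4, 6; week 7 is after treatment) |

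The last reading is improbable. If those weeks belonged to craving, the γ-GT and blood alcohol clause would have no times and the word weekly would have no meaning. A full stop after weekly restores the sense.

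**What each reading supports**

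1. Under the first reading, the t test of Section 3.8 can be done. The mixed regression over the study could also use follow-up PACS scores, but it would have one on-treatment value. A comparison over the course of treatment, as Section 3.2 defines the outcome, has no data from weeks 1 to 5.
2. Under the second reading, both analyses can be done, but the text does not say which one decides the co-primary.
3. Under the third reading, two measures could serve as the co-primary, and the text does not choose between them.

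Every reading leaves at least one of scale, visits and primary analysis open.

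**Illustration of what weekly scores could add**

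Assumptions, none of them from the documents: equal correlation r between any two occasions, r from 0.5 to 0.8, equal variance at each occasion (set to 1), and the same treatment effect in every week.

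- Variance of the mean of six scores: V = (1 + 5r)/6.
- Baseline-adjusted variance of that mean: V − r².
- Baseline-adjusted variance of the week-6 score: 1 − r².
- Ratio: (V − r²)/(1 − r²).

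| r | V | V − r² | 1 − r² | Ratio |
|---|---|---|---|---|
| 0.5 | 0.583 | 0.333 | 0.750 | 0.44 |
| 0.6 | 0.667 | 0.307 | 0.640 | 0.48 |
| 0.7 | 0.750 | 0.260 | 0.510 | 0.51 |
| 0.8 | 0.833 | 0.193 | 0.360 | 0.54 |

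The two quantities are different estimands: an average over treatment and a value at its end. The ratio shows scale only, and the point does not rest on it.

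**The case against.** The strongest reply is that the sections can be read together. The list in Section 3.3 also contains adverse events (COMBINE SAFTEE), and Section 3.2 has adverse events evaluated weekly in the same clause as craving. The list is therefore evidently not the complete schedule for every item in it. The natural picture is a full battery at weeks 0 and 6 and in follow-up, with craving and adverse events also recorded weekly. PACS is the only craving scale in the text and in the Figure 1 legend, so the self-rating scale of Section 3.2 is probably PACS. Figure 1 is the schedule of assessments and may settle the visits, but it is not shown here.

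Much of this stands, and it rules out three stronger conclusions that a reader might draw.

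- *That the two schedules flatly contradict each other.* Section 3.3 does not say that PACS is given at weeks 0 and 6 only, it adds follow-up, and Section 3.2 does not name PACS. A strict contradiction is not shown.
- *That the co-primary cannot be computed.* A week-6 PACS comparison can be computed even with two treatment-period scores, and Section 3.8 plans one.
- *That about half of the information is discarded.* The variance ratio compares two estimands under assumed correlations and a constant effect. If the effect builds up over treatment, averaging in the early weeks would dilute it. The ratio also has no bearing if PACS is in fact collected weekly.

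The reply does not supply the missing link. The text never says that the weekly craving rating is PACS, it ties PACS in Section 3.8 to baseline and week 6, and it leaves resistance without an instrument and the two analyses unranked.

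**Conclusion.** The point holds as an unresolved specification of a primary outcome. Followed literally, the text gives one on-treatment PACS score after baseline for an outcome defined over the course of treatment, against six under the weekly reading, and it leaves two craving analyses in competition. The conclusion rests on the wording of Sections 3.2, 3.3 and 3.8, and on no assumed figure. It is limited by Figure 1 not being visible: if the figure shows weekly PACS, the visits are settled there, but the wording of Section 3.3 and the choice of primary analysis would still need attention. The correction should be made before or early in data collection, because missed scores cannot be recovered.

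**What to change.** 1. In Sections 3.2 and 3.3, and in Figure 1 if it differs, name the PACS total score as the single primary craving measure, self-completed at week 0 and at each weekly contact in weeks 1 to 6. Keep the follow-up assessments as planned.
2. In Section 3.2, end the sentence after the weekly evaluation of craving and adverse events, so that the listed weeks attach clearly to γ-GT and blood alcohol, if that is what is meant.
3. In Section 3.8, replace desire and resistance with the PACS total score and name one analysis as primary. One option is the mixed model over weeks 1 to 6 adjusted for baseline, with the week-6 comparison as supportive. Making the week-6 comparison primary would also remove the ambiguity, but the definition in Section 3.2 would then have to be changed to match.

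The cost is protocol wording and a short self-completed form at up to five contacts (weeks 1 to 5). Those contacts already exist: Section 3.1 has weekly psychosocial treatment, and Section 3.2 has a weekly physical examination and breath alcohol test. If PACS is already completed weekly, the cost is wording alone.
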